### Sample size estimation

Based on prior outpatient footfall data from participating PHCs, it is estimated that roughly 178 adult outpatients will attend each PHC per month; thus, over a 12-month period of delivery of the Enhanced Implementation Support strategy, there will be approximately 14,994 patients attending facilities in each arm. Assuming about 10% of these patients [based on prior case detection data in the region (14)] will refuse screening or will be excluded at the discretion of the ANM/nurse, the resulting estimates work out to about 13,494 outpatients available for screening in each arm. This sample size will allow us to detect a 15% difference in the proportion of PHQ-2 screenings between arms, assuming that 10% of patients are screened in the Routine Implementation Support Arm, at 80% power, an inter-cluster coefficient of variation of 0.5 (calculated from background facility data on adult outpatient footfall and existing NCD screening rates) and an intra-cluster correlation (ICC) of 0.05 (52).

Proportions (and not numbers of screenings) will be used to account for the between-facility variation in outpatient footfall.

The earlier PRIME study conducted in the same region achieved a 12% depression screening rate in its facility detection survey component (14), and assuming an additional contribution by the various components of enhanced implementation support (i.e., fortnightly coaching calls, WhatsApp support and monthly peer-learning conferences) to further increase the depression screening rate, we will hypothesize a 25% screening rate in the intervention arm, or a 15% between-arm difference in screening rates. We have referred the formula for calculating sample size for parallel cluster randomized controlled trials with fixed number of clusters (*n* = 14 in this study) by Hemming et al. 2020 (52).

### Facility randomization

As outlined in the CONSORT diagram in Figure 3, PHCs will be randomized to the “Enhanced Implementation Support” intervention or “Routine Implementation Support” control condition using 1:1 random allocation. Stata statistical software will be used to prepare the allocation table, to assign and monitor the allocation of PHCs. Prior studies have shown that facility size may affect implementation of mental health services, as large facilities may have more capacity for flexibly utilising resources during implementation of a new evidence-based practice compared to small facilities (53). Therefore, facilities will be stratified by number of monthly outpatient attendees, as this variable can serve as a proxy for facility size, and furthermore, busier clinics may face distinct implementation challenges compared to quieter clinics (e.g., a private location for screening). Drawing from facility characteristics, and based on probability proportional to facility size sampling, the expected contributions (percentages) by each facility per arm per month was calculated. These details will be used to define the strata as either “high” or “low” patient footfall facilities, to ensure balance in facility size between arms.

**Figure 3 F3:**
[figure not shown]
Trial CONSORT diagram.

### Blinding

It will not be possible to blind the PHC staff to arm allocation, and the research team will also not be blind to arm allocation. For patients who enrol, they will not be informed about the allocation of their respective facility, and it is unlikely that they would become aware of arm allocation. Study outcome assessors collecting outcomes from patients, and the statistician who will analyze the final outcome data will be blinded to arm allocation. There will be complete separation between the team members involved in delivering the enhanced implementation support intervention, and those involved in administering the outcome assessments; for example, the implementation support team will be based in Sangath Bhopal office and outcome assessors will work from the district office (rural), closer to the study population.

### Statistical analysis

All analyses of implementation outcomes will be intention-to-treat comparisons between arms. Generalized linear regression models with a log link will be used to compare facility-level implementation outcomes, including the primary outcome of proportion of patients screened on the PHQ-2. ANCOVA analyses will be conducted for comparing secondary implementation outcomes between arms. Time by study arm interactions will be explored using a growth curve model to inspect non-linear trends in the progress of the screening, number of patients who screen positive, referral to MO and treatment initiation. Descriptive statistics will be used for comparing exploratory measures of facility readiness and context assessment between arms. The process indicators from the PDSA coaching sessions will be used for descriptive analysis, to quantitatively assess fidelity to the protocol for Enhanced Implementation Support. Logistic regression models will be used to compare the proportion of patients who remit on the PHQ-9, defined as score <5, between arms at 3-month follow-up. Possible covariates will be entered into the models, including age or gender of the patients, as well as adjusting for cluster effects. Linear regression models will be used to assess differences in the change in disability (WHODAS 2.0) and anxiety (GAD-7) outcomes at 3-month follow up, with baseline values as covariates to adjust for any baseline inter-cluster differences. Stata version 17.0 will be used for all statistical analyses and *p*-values <0.5 will be considered statistically significant.

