**Methods:**

Employing a cluster-randomized hybrid type-III implementation trial design, 14 primary care facilities in Sehore district, Madhya Pradesh, will implement a collaborative depression care package based on the WHO's mhGAP program. Facilities will be randomized to either Enhanced Implementation Support or the Routine Implementation Support control condition. Enhanced Implementation Support consists of remote coaching and technical assistance, supplemented with in-person visits, and guided by the Plan-Do-Study-Act implementation cycles. The primary implementation outcome is the proportion of outpatients screened for depression by facility staff, with secondary outcomes including the proportions of outpatients who screen positive for depression, are referred to the medical officer, and initiate treatment. Secondary patient outcomes include proportion of patients who achieve reduction in depression symptom severity at 3-month follow up. Acceptability, feasibility, and fidelity of the depression care package will be assessed through routine observations collected during field visits, facility audits, and qualitative exit interviews with facility staff. Costs of delivering the Enhanced Implementation Support strategy will also be estimated.

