### Study objectives and hypotheses

The objective of this hybrid type III cluster-randomized controlled superiority trial is to evaluate whether a remote coaching implementation support strategy, referred to as “Enhanced Implementation Support”, is superior when compared to routine support, referred to as “Routine Implementation Support”, in facilitating the delivery of depression care in primary care facilities in rural India. This will be ascertained by measuring the proportion of outpatients screened for depression, number of cases of depression detected, and number of patients referred to the MO and initiated on treatment at the participating primary care facilities. It is hypothesized that Enhanced Implementation Support will be superior to Routine Implementation Support in increasing the proportion of outpatients screened for depression using the two-item Patient Health Questionnaire (PHQ-2) (27) by ANMs/nurses. It is also hypothesized that Enhanced Implementation Support will be superior to Routine Implementation Support in increasing the number of cases of depression detected, and number of patients referred to the MO and initiated on treatment.

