### Outcome measures

#### Primary implementation outcome

Table 3 lists the study implementation outcomes. For the primary implementation outcome, the proportions of outpatients screened on the PHQ-2 by the ANM/nurse will be compared between study arms. The denominator for the proportion of outpatients screened will be calculated as the total number of adult outpatients for the NCD care program attending the PHCs during the trial period. ANMs/nurses will use a Screening Record Register to document the number of patients screened. The facilities will send the screening data to the data manager on a weekly basis.

**Table 3 T3:** Implementation outcomes.

Measure	Source	Description	Rationale for selection	Hypothesis	Timeline
Primary outcome					
Comparison of Proportion of persons screened on PHQ-2	Screening record register data on primary health center implementation activities, filled regularly by the ANM/nurse	The percentage of adult individuals attending primary health centers who are screened on PHQ-2 by the ANM/nurse.	Screening for depression on PHQ-2 is the gateway for initiating depression care.		Collected/reviewed weekly over the trial duration
Secondary outcomes					
Acceptability: Proportion of patients who refuse to be screened for depression	Screening Record Register data on primary health center implementation activities, filled regularly by the ANM/nurse	The percentage of adult individuals attending primary health centers who refuse to be screened on PHQ-2 by the ANM/nurse will be compared between the trial arms.	Screening for depression on PHQ-2 is the rate-limiting step in the entire patient flow at a primary health center, therefore, assessing the extent of refusal of being screened is important for understanding the acceptability of implementation of depression screening.	The proportion of persons who refuse to be screened on PHQ-2 will be significantly lesser in the intervention arm or in facilities receiving enhanced implementation support, than those receiving routine support (control arm)	Collected/reviewed weekly over the trial duration

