Adoption: Proportion of patients initiated on treatment	Screening Record Register data on primary health center implementation activities, filled regularly by the ANM/nurse	The percentage of adult individuals attending primary health centers who are screened positive on PHQ-2 by the ANM/nurse, referred to the MO and initiated on treatment by the MO i.e., provision of psychoeducation and appropriate antidepressant medication and/or referral to the Healthy Activity Program delivered by the ASHA worker, and/or referral to a specialist at the District Mental Health Program or Community Health Centre or private clinic.	Treatment initiation by the medical officer is a comprehensive process indicator as it covers the preceding steps in the patient flow at a primary health center. In addition, this measure reflects the downstream effect of implementation support strategies on adoption of collaborative care package for depression care.	The proportion of screened positive cases initiated on treatment will be significantly greater in the intervention arm or in facilities receiving enhanced implementation support, than in the control arm or in facilities receiving routine support.	Collected/reviewed weekly over the trial duration

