#### Secondary implementation outcomes

As outlined in Table 3, secondary implementation outcomes will be guided by the heuristic defined by Proctor et al, 2010 (19), and will be assessed using facility-level administrative data and the indicators captured in the screening record register (Table 2), and supplemented with qualitative semi-structured interviews with the facility teams. Implementation metrics will include number of patients who refuse screening, number of patients who screen positive for depression, number of screen positive patients who are referred to the MO and number of patients who are initiated on treatment. Treatment initiation following referral to the MO is an important adoption outcome, and can involve provision of psychoeducation, prescription of antidepressant medication, referral to the brief psychosocial intervention (i.e., HAP) delivered by ASHAs, and/or referral to a specialist at the District Mental Health Program, Community Health Centre or private clinic.

The costs of delivering the Enhanced Implementation Support strategy in the intervention arm PHCs will be collected and categorized into the six building blocks of a health system based on the WHO's health system framework (45). This will include spending on health workforce for participating in the Enhanced Implementation Support strategy activities, such as time required to moderate (for the coaches) and participate (for the ANM/nurse) in the coaching sessions; and information technology, such as internet costs or phone bills for engaging in the coaching sessions. This data will be captured via time logs, payroll, and expense reports. Facility staff salaries will be collected from the National Health Mission reports on salary range for various health personnel in public health facilities. To clarify, the cost analysis will not evaluate the cost-effectiveness or involve a comparison of costs between the study arms because we are not able to collect cost data from the control arm given the irregular or need-based format of routine district team's support to the clinics for delivering depression care (refer, “Routine implementation support”), and because there is no additional implementation support being provided by our team for which the costs could be collected. We will be assessing only the cost of delivery of Enhanced Implementation Support strategy among the intervention arm clinics.

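### Secondary implementation outcomes are stated as numbers in some places and proportions in others; one scale and one denominator per outcome are needed, because raw counts carry clinic volume

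*Protocol article*

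**What the plan says.** **Numbers.** Study objectives and hypotheses states the secondary hypothesis as superiority in "increasing the number of cases of depression detected, and number of patients referred to the MO and initiated on treatment". Secondary implementation outcomes lists metrics the same way: "Implementation metrics will include number of patients who refuse screening, number of patients who screen positive for depression", followed by the numbers referred and initiated. Statistical analysis describes the exploratory time-by-arm work as "using a growth curve model to inspect non-linear trends in the progress of the screening, number of patients who screen positive"; referral and initiation follow in the same list without a scale.

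**Proportions.** The abstract has "secondary outcomes including the proportions of outpatients who screen positive for depression, are referred to the medical officer, and initiate treatment". Table 2 lists screen positives as a proportion of patients and referral as a proportion of cases. Table 3 gives two proportion hypotheses: "The proportion of persons who refuse to be screened on PHQ-2 will be significantly lesser in the intervention arm" and "The proportion of screened positive cases initiated on treatment will be significantly greater in the intervention arm".

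**The stated reason for proportions.** Sample size estimation says: "Proportions (and not numbers of screenings) will be used to account for the between-facility variation in outpatient footfall". The sentence is about screenings, that is, the primary outcome.

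**Related provisions.** Facility randomization stratifies on high or low monthly footfall. Table 2 also lists total adult outpatient attendance as an indicator, so a denominator is available.

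**The concern.** Whoever writes or reads the final analysis cannot tell from the article which scale decides the secondary hypotheses. Two things are at stake.

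First, a count is a rate multiplied by volume. Positives, referrals and initiations come from the same attendees as screenings, so the footfall argument made for screening applies to them equally. With only 7 facilities per arm, an arm that happens to hold busier clinics will show more cases and more referrals at identical quality of care.

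Second, the scales answer different questions. If coaching raises screening and nothing downstream changes, the number referred rises but the proportion of cases referred does not. The two versions of the hypothesis can then lead to opposite conclusions.

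**Working it through.** **1. Scale by outcome and place**

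| Outcome | Objectives | Secondary outcomes text | Growth curve | Abstract | Table 2 | Table 3 |
|---|---|---|---|---|---|---|
| Refusal | not stated | number | not listed | not listed | proportion of patients | proportion of adults attending |
| Screen positive | number | number | number | proportion of outpatients | proportion of patients | no row |
| Referral to medical officer | number | number | no scale given | proportion of outpatients | proportion of cases | no row |
| Treatment initiation | number | number | no scale given | proportion of outpatients | by treatment type, proportion of cases | description: adults attending; hypothesis: screened-positive cases |

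Detection and referral have their formal hypothesis only as numbers. Initiation has it both ways. Initiation also has two denominators within one row of Table 3, and referral has one denominator in the abstract and another in Table 2.

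**2. The plan's own figures**

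Attendance per arm: 178 × 12 × 7 = 14,952, against 14,994 stated (178.5 × 84 gives 14,994 exactly). Available for screening: 14,994 × 0.9 = 13,494.6, against 13,494 stated.

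Power: cluster size m = 13,494 / 7 = 1,928. Design effect = 1 + ((1 + 0.5²) × 1,928 − 1) × 0.05 = 121.4. Effective n = 13,494 / 121.4 = 111 per arm. For 10% v 25%, power is 78.7% (t, 12 df) to 84.2% (pooled z), with two-sided alpha 0.05 assumed. The stated 80% reproduces. It concerns the primary outcome, and this point does not depend on it.

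**3. How far volume alone can move a count**

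Assume equal underlying rates in both arms. The expected ratio of proportions is 1.0 whatever the footfall; the expected ratio of counts is the ratio of arm footfall totals. If facility footfall has coefficient of variation 0.5, the SD of the log ratio without strata is about √(2 × 0.5² / 7) = 0.267, so its 95% limits are about exp(±1.96 × 0.267) = 0.59 to 1.69. Simulation with lognormal footfall, 14 facilities, 7 v 7:

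| CV | Strata (low/high) | 95% range of footfall ratio | Differ by >25% | Differ by >50% |
|---|---|---|---|---|
| 0.5 | none | 0.59–1.68 | 39.5% | 12.3% |
| 0.5 | 7/7 | 0.67–1.49 | 27.6% | 4.9% |
| 0.5 | 6/8 | 0.69–1.45 | 23.3% | 3.5% |
| 0.3 | none | 0.73–1.37 | 16.2% | 1.2% |
| 0.3 | 7/7 | 0.79–1.26 | 6.4% | 0.1% |
| 0.3 | 6/8 | 0.81–1.24 | 4.0% | 0.0% |

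Stratification narrows the range but does not close it.

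**4. How the choice of scale changes the hypothesis**

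Take A attendees per arm, positivity q among those screened and referral r among positives, with q and r equal in both arms and the plan's 10% and 25% screened. Numbers referred are 0.10·A·q·r and 0.25·A·q·r, a ratio of 2.5. The proportion of attendees referred also has ratio 2.5. The proportion of cases referred is r in both arms, a ratio of 1.0.

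**5. Whether a weekly per-case denominator works**

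Weekly attendance is 178 × 12 / 52 = 41 per facility. At 10% screened, that is 4.1. With an assumed positivity of 10 to 20%, expected positives are 0.41 to 0.82 per facility-week. Under a Poisson assumption, exp(−0.82) = 44% to exp(−0.41) = 66% of control facility-weeks have no case. By month the expected number is 1.78 to 3.56, and 17% to 3% have none. By quarter the expected number is at least 5.34, and under 1% have none.

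**The case against.** Much of the case on the other side stands.

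- **A reader might infer that the plan has chosen counts for all secondary hypotheses.** The documents do not support that. Table 3, which has the hypothesis column, uses proportions for refusal and initiation, and the abstract and Table 2 also use proportions. The defect is a conflict of scale.
- **A reader might say the plan breaks its own rule.** The sentence on proportions is worded for screenings and sits in the sample size section. Extending it to later steps of the pathway is an inference, though a natural one.
- **A reader might take the chance of unequal volume as a bias or a false-positive rate.** Under the same assumptions (CV 0.5), totals differ by more than 20% in about 33 to 37% of stratified allocations, but that describes volume only. Facilities are randomized, so volume variation enters the between-facility variance, and a valid cluster-level test keeps its error rate. The main cost is precision and, in a single realized trial, interpretation.
- **A reader might carry these figures over to the time-by-arm term.** They concern total levels. Facility intercepts, if fitted, would absorb stable volume, and on a log scale a season shared across one district largely cancels between arms. On a raw-count scale a busier clinic still shows a steeper slope for the same change in rate, but no size for that can be given from the article.
- **The growth-curve wording is thin evidence.** It attaches a number clearly only to screen positives, and the analysis is exploratory. Offsets and random effects may be in the analysis plan, which is not shown. Likewise the ANCOVA could adjust for the footfall recorded at recruitment, although the article does not say so.

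An unseen analysis plan could settle the model. It would not remove the conflict between the hypotheses as published.

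**Conclusion.** The concern holds as an inconsistency of scale and denominator in the secondary implementation outcomes. It is minor: the primary outcome is defined as a proportion and is not affected.

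If counts were compared as worded, footfall alone would give a 95% range for the arm ratio of about 0.67–1.49 with two strata at a coefficient of variation of 0.5, and about 0.8–1.25 at 0.3. This rests on three assumptions: that 0.5 describes footfall (the article derives it from footfall together with existing screening rates for non-communicable diseases), that footfall is lognormal, and that the strata are 7/7 or 6/8, which the article does not state. The 2.5-fold versus 1.0 contrast for referral needs only the plan's screening rates and equal downstream steps.

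**What to change.** 1. Restate as proportions the hypotheses in the objectives, the metrics under Secondary implementation outcomes and the growth-curve outcomes, with one named denominator for each.
2. For detection, use adult attendance, the same denominator as the primary outcome. Settle that denominator first: the text ties it to outpatients of the non-communicable disease program, while Table 3 says adults attending.
3. For treatment initiation, reconcile the two denominators in Table 3 (adults attending v screened-positive cases). For referral, reconcile the abstract with Table 2.
4. Where counts are modelled, use a log-attendance offset or a binomial model, with facility effects. Avoid a weekly offset of log screen-positive cases: it is undefined in weeks with none and conditions on a quantity the intervention is meant to change. For per-case outcomes, use periods long enough to avoid zero denominators; on the figures above, quarters rather than weeks.
5. Label any per-case proportion as conditional on a group formed after randomization, and report raw counts descriptively.

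The cost is wording and a model term. Attendance is already an indicator, but weekly transmission is stated for screening data and not for attendance, so its time resolution should be confirmed. The article describes the primary analyses as still to follow. If that remains so, date and record the change before any arm comparison is seen.

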Facility readiness scores and predictors of adoption of collaborative care package for depression	Health Facility Context Assessment (Atlas Initiative Context Assessment Tool, Ariadne Labs), which includes the ‘progress’ survey and the ‘post-implementation’ survey	We have adapted the Atlas toolkit and will use the *Progress* and *Post-Implementation* surveys for trial requirements. The *Progress survey* for frontline staff and facility-leader (medical officer) is a 57-item tool, and *post-Implementation survey* is a 55-item tool. The target audience of these two surveys will include leaders, such as facility-level medical officers in-charge, and frontline healthcare workers involved in delivering the intervention such as ANMs/nurses. Implementation strategy and therefore, look at facility-level factors that are more dynamic than those in the Foundation Survey. The target audience will be similar to that of the Foundation Survey.	In a nutshell, the Progress Survey taps the internal culture of the organisation, which is not expected to change soon after the roll out of the implementation support strategy. The Post-Implementation Survey will assess the need for modifications to the implementation support strategy. The “Progress” Survey will aim to assess the key contextual factors that impact the implementation of a healthcare intervention and should be considered when making decisions about the readiness to implement, the implementation strategy, and possible adaptations to the designed intervention before its delivery. 2. The “Post-Implementation” Survey: The Launch Survey will examine the need to make modifications to the implementation strategy and therefore, look at facility-level factors that are more dynamic than those in the Foundation Survey.	Facilities that show greater readiness scores (regardless of arm allocation) will show greater adoption of the depression care program, resulting in improved implementation outcomes.	The Progress survey will be administered towards the end of embedding as a baseline. The Post-implementation survey will be administered about a month before wrap-up of trial activities.

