### Exploratory outcomes

The Organizational Readiness for Implementing Change (ORIC) (49) will be used to assess readiness of the PHCs for implementing the depression care package. This 12-item survey is based on Weiner's theory of organizational readiness for change and covers two core constructs—change commitment (5 items) and change efficacy (7 items). The Atlas Initiative Toolkit will be used to assess facility-specific implementation factors (50). The toolkit includes two surveys, beginning with the Progress Survey followed by the Post-Implementation Survey. The surveys are based on an organizational readiness heuristic, abbreviated as R = MC2 (51), which defines organizational readiness for an innovation (R) as a function of three components: motivation to implement an innovation (M), the general capacities of an organization (C), and the innovation-specific capacities needed for a particular innovation (C). The surveys were translated and adapted for use in Madhya Pradesh, India, and will be collected from the MOs and ANMs/nurses involved in delivering depression care. The Progress Survey will be collected before trial launch to assess contextual factors that may impact the readiness to implement depression care. This survey captures the internal culture of the facility, which is not expected to change soon after initiating the Enhanced Implementation Support strategy. The Post-Implementation Survey will be collected from the same facility staff about one month before the end of the 12-month active intervention phase to assess the need for modifications to the implementation strategy.

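### The only analysis stated for the readiness measures, a descriptive comparison between arms, cannot address Table 3's hypothesis that readier facilities adopt more

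*Protocol article*

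**What the plan says.** In the exploratory rows of Table 3, the outcome is titled "Facility readiness scores and predictors of adoption of collaborative care package for depression". The hypothesis is the same for the Atlas surveys and for ORIC: "Facilities that show greater readiness scores (regardless of arm allocation) will show greater adoption of the depression care program, resulting in improved implementation outcomes".

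The Exploratory outcomes section describes the instruments. ORIC, for example, "will be used to assess readiness of the PHCs for implementing the depression care package". It gives no analysis.

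The Statistical analysis section assigns one analysis to these measures: "Descriptive statistics will be used for comparing exploratory measures of facility readiness and context assessment between arms". For implementation outcomes in general it says: "All analyses of implementation outcomes will be intention-to-treat comparisons between arms". On covariates it says: "Possible covariates will be entered into the models, including age or gender of the patients, as well as adjusting for cluster effects". Readiness is not named as a covariate or predictor in any model.

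**The concern.** The hypothesis is about an association across facilities: does a facility with a higher readiness score show more adoption, once arm is set aside? The stated analysis asks whether the two arms differ in readiness. These are different questions with different null hypotheses, and an answer to the second does not bear on the first.

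If the article's analysis section is followed as written, the report will contain a table of readiness by arm and nothing that relates readiness to adoption. The outcome's own title presents readiness as a predictor of adoption, so that is the result a reader would look for.

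**Working it through.** The plan gives no figure on this point, so there is none to reproduce. The check compares the hypothesis with the analysis, then asks how precise a matching analysis could be.

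**1. What each quantity depends on.** For each facility let R be the readiness score, A the adoption outcome and T the arm (0 or 1). Table 3's hypothesis concerns the slope β in

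A = α + τT + βR + error, with the claim β > 0.

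The planned comparison is the difference in mean readiness, D_R = mean(R | T=1) − mean(R | T=0). A does not appear in D_R, so D_R has the same distribution whatever β is. It can be zero when β is large, and large when β is zero.

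**2. Whether setting it beside the main result helps.** The arm difference in adoption is D_A = τ + β·D_R, apart from error. That is one equation with two unknowns, τ and β, so two pairs of arm means cannot separate them. Estimating β needs the variation in readiness among facilities within arms.

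**3. Whether another sentence in the article supplies the analysis.**
- Implementation-outcome analyses: declared to be comparisons between arms.
- Growth curve model: time-by-arm interactions only.
- Covariates: patient age or gender, cluster effects, and baseline WHODAS 2.0 and GAD-7 values. The list is not closed, but readiness is not on it.
- Exploratory outcomes section: instruments and timing only.

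None relates readiness to adoption.

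**4. Which readiness score could act as a predictor.** Table 3 times ORIC and the Atlas Progress survey towards the end of embedding. It times the second ORIC and the Atlas Post-Implementation survey about a month before wrap-up; the Exploratory outcomes section puts the latter about a month before the 12-month active phase ends. On either timing, at least about 12 − 1 = 11 months of that phase come before the later score, so it follows most of the adoption it would be used to predict. Only the end-of-embedding score can serve. By the Study procedures section that score also comes after randomisation, at a time when intervention facilities were already being trained in the strategy. Adjustment for arm is therefore needed.

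**5. Precision with 14 facilities.** The number of facilities comes from the Sample size estimation section, which works from a "fixed number of clusters" of 14. The article prints its significance threshold as 0.5, so a two-sided 0.05 is assumed here. By Fisher's z, without covariates, the standard error is 1/√(14 − 3) = 1/√11.
- Correlation for 80% power: tanh((1.960 + 0.842)/√11) = tanh(0.845) = 0.69.
- Power at r is Φ(atanh(r)·√11 − 1.960). This gives 18% at r = 0.3, 45% at r = 0.5 and 82% at r = 0.7.

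Adjusting for arm costs one degree of freedom, so √11 becomes √10:
- Correlation for 80% power: tanh(2.802/√10) = tanh(0.886) = 0.71.
- Interval if the observed partial correlation were 0.5: 0.549 ± 1.960/√10 = 0.549 ± 0.620 on the z scale, which is −0.07 to 0.82 after back-transformation.

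The values of r are assumptions; the article gives none.

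**The case against.** The strongest reply is that this is a condensed article. The Ethical considerations section mentions a statistical analysis plan, which is not shown, and a secondary look at an exploratory predictor is the kind of detail such a plan often holds. A reader might infer that the readiness hypothesis will never be examined. The article does not support that, because it nowhere says the descriptive comparison is the only use of the readiness data. This limits the point to the article, but it does not remove it. The article is not silent: it names an analysis for these measures, and that analysis does not match its own hypothesis.

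Second, the outcome is exploratory, the hypothesis is absent from the Study objectives and hypotheses section, and the Exploratory outcomes section gives the surveys a contextual purpose that description serves well. This stands. It makes the matter minor and makes rewording the hypothesis a full remedy.

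Third, a reader might want to express the mismatch as lost power, by setting a between-arm test of readiness against a regression of adoption on readiness. That is not supported either. The plan specifies description and no test, the two procedures address different nulls, and any effect sizes would be invented.

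Fourth, one might expect an arm difference in readiness to be read as readiness driving adoption. The article proposes no such inference, so this remains only a possible misreading.

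**Conclusion.** The point holds for the article as published. Table 3's readiness hypothesis and the one analysis stated for the readiness measures do not match, and the stated comparison cannot support or refute the hypothesis. That conclusion comes from reading the two places together and needs no numerical assumption.

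Severity is minor. No primary, secondary or patient outcome is touched. A matching analysis could only be exploratory: at the assumed two-sided 0.05 level, about 80% power is reached only near r = 0.7, so failure to find an association would say little. Whether the unseen analysis plan already fills the gap cannot be judged from this document.

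**What to change.** Either of two changes resolves it.

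**Add the matching analysis.** Keep the between-arm readiness table and label it descriptive only. Then add to the Statistical analysis section an exploratory facility-level analysis across the 14 centres:
- Predictor: the end-of-embedding score, with Atlas Progress and ORIC analysed separately. Do not use the end-of-trial scores as predictors.
- Outcomes: the adoption outcome (proportion initiated on treatment) and the proportion screened.
- Adjustment: arm.
- Reporting: slopes or partial correlations with 95% confidence intervals, labelled exploratory.

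**Or reword the hypothesis.** Change the Table 3 text, and the outcome's title, to what a descriptive comparison of readiness between arms can show.

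The first option costs a short addition to the text and 2 instruments × 2 outcomes = 4 small regressions on data the trial already planned to collect. The downside is wide intervals. The second costs only an edit. The Trial status section places the primary analyses after closeout, so at the time of writing either change could still be made before them.
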